#### Healthy Lifestyle Change

So that lifestyle behaviors are quantified on a common metric, we will generate z-scores reflecting each participant's average daily fruit/vegetable intake, saturated fat intake, daily physical activity, and daily targeted sedentary activity relative to the sample distribution at baseline. Z-scores will be standardized such that positive values indicate more healthful behavior change. Scores will be averaged across all four behaviors (FV, Fat, Sed, and PA) to derive a composite index that expresses the average healthy lifestyle change achieved by each participant.

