### Sample Size and Power

The effect size calculations assume a two-sided alpha set at .05 and were estimated for a power of .85.

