#### Primary Aim: Healthy Lifestyle

The outcomes for the primary aim are the z-scores for fruit and vegetables (FV), saturated fat (Fat), physical activity (PA) and sedentary activity (Sed) separately and averaged to form the composite healthy lifestyle score. Using pilot data to compare any one treatment condition to the other three, we found average effect sizes equal to .66, .63, .21 and .47 for change in FV, PA, Sed, and Fat, respectively. Therefore, we anticipate that we will have effect sizes approximately equal to .5 for the three comparisons on each outcome variable. Given an effect size of .5, a total of 200 participants, 50 per group, will yield adequate power for testing the three contrasts.

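### The .85 power for the composite primary outcome rests on an average of component effect sizes, which is not the composite's effect size

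*Protocol article*

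**What the plan says.** The section Healthy Lifestyle Change defines the primary outcome: "Scores will be averaged across all four behaviors (FV, Fat, Sed, and PA) to derive a composite index". Under Analytic Plan, Primary Aim, that composite is the dependent variable of the mixed model and of the three planned comparisons.

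Under Sample Size and Power: "The effect size calculations assume a two-sided alpha set at .05 and were estimated for a power of .85". The Primary Aim subsection there lists as outcomes the four z-scores, each on its own and averaged into the composite. Its evidence comes from a pilot contrast of a single arm with the remaining arms: "we found average effect sizes equal to .66, .63, .21 and .47 for change in FV, PA, Sed, and Fat, respectively". From these it infers an effect of roughly .5 for the three comparisons on every outcome variable, and concludes: "Given an effect size of .5, a total of 200 participants, 50 per group, will yield adequate power for testing the three contrasts".

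No pilot effect is given for the composite. No signs, no per-arm values and no correlations between behaviours are given either.

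**The concern.** The figure of .5 matches the mean of the four component effects, and it is then applied to the composite. The mean of four standardised effects is not the standardised effect of the mean. The latter has a numerator in which components can cancel or add up, and a denominator that depends on how strongly the components correlate.

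The design makes cancellation plausible. Each arm targets two behaviours, and each behaviour is targeted in two of the four arms. On a behaviour that an arm targets, only one of its three comparators shares the target. On a behaviour that it does not target, two of the three comparators do. An arm may well be ahead on two behaviours and behind on two, in which case the composite sets gains against losses.

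The composite contrasts are the primary test. If their true effects are much smaller than .5, a null result would say little about whether the prescriptions differ, yet the stated power would invite the reading that they do not.

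**Working it through.** **Inputs from the article.** Two-sided alpha .05; target power .85; 50 per group; one condition against the other three, so 50 vs 150; pilot effects FV .66, PA .63, Sed .21, Fat .47.

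**Step 1: reproduce the plan's figure.** The standard error of a one-versus-three contrast in SD units is sqrt(1/50 + 1/150) = .1633. At d = .5 the noncentrality is .5/.1633 = 3.06. Power is .865 by the normal approximation and .861 by the noncentral t. The stated .85 is reproduced. The smallest d that gives .85 is (1.960 + 1.036) × .1633 = .489.

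**Step 2: where .5 comes from.** (.66 + .63 + .21 + .47)/4 = 1.97/4 = .4925.

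**Step 3: the effect size of the composite.** Let s_k = +1, 0 or −1 be the direction of component k in a given arm, d_k its magnitude, and r a common correlation between component changes. With component SD 1,

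d_composite = [Σ s_k d_k / 4] / sqrt((1 + 3r)/4).

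The denominator is .500 at r = 0 and .791 at r = .5. The article gives neither s_k nor r, so three sign patterns are shown. The magnitudes are the pilot averages, assumed to apply in every arm.

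**Step 4: what the design suggests about signs.** Suppose a behaviour changes by T in arms that target it and by C in arms that do not. The contrast is T − (T + 2C)/3 = 2(T − C)/3 for a targeting arm, and C − (C + 2T)/3 = −2(T − C)/3 for a non-targeting arm. In this simple model the signs are opposite whenever T exceeds C. If C differs between arms, this need not hold.

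**Step 5: power at 50 vs 150, two-sided .05 (r = 0, then r = .5).**

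| Arm | Pattern for untargeted behaviours | Numerator | d | Power |
|---|---|---|---|---|
| FV up, PA up | reversed | (.66+.63−.21−.47)/4 = .1525 | .305, .193 | .46, .22 |
| Fat down, PA up | reversed | (.47+.63−.66−.21)/4 = .0575 | .115, .073 | .11, .07 |
| FV up, Sed down | reversed | (.66+.21−.63−.47)/4 = −.0575 | −.115, −.073 | .11, .07 |
| FV up, PA up | neutral | (.66+.63)/4 = .3225 | .645, .408 | .98, .70 |
| Fat down, PA up | neutral | (.47+.63)/4 = .2750 | .550, .348 | .92, .57 |
| FV up, Sed down | neutral | (.66+.21)/4 = .2175 | .435, .275 | .76, .39 |
| Any one favoured arm | all four favourable | 1.97/4 = .4925 | .985, .623 | >.99, .97 |

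The two figures for the FV-up, Sed-down arm under reversal are for an effect in the unfavourable direction.

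**Step 6: the components themselves.** At each behaviour's own pilot effect, power is .98 (FV), .97 (PA), .82 (Fat) and .25 (Sed). The claim of about .5 on every outcome therefore conflicts with the article's own .21 for Sed, without any added assumption.

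**The case against.** A reader might infer that the component effects do have opposite signs within each arm, and so that the trial could not have shown a difference. The article does not support either statement. It reports no signs and no per-arm values. For a single outcome, one-versus-three contrasts sum to zero across four equal arms, so an average taken over all four arms must be of magnitudes. That says nothing about signs across outcomes within one arm, and the article does not say which arms were averaged. The design can also detect about .49 SD of composite change at .85 power. What lacks support is the assumed effect, not the ability to detect one of that size.

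It is also fair to say that the reversed pattern assumes away what the trial sets out to test. The behavioural economic hypothesis expects untargeted behaviours to improve too, and power is normally computed under the alternative. Moreover, the three hypotheses compete, so low power for arms that are not the best is no defect in itself. These points stand. They are why the full range is shown, including patterns in which power is at or above .85.

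They do not rescue the stated figure. The article offers no adult estimate of collateral change large enough to settle the signs. Its Background cites a ratio of about 1:3 for activity in children, finds no apparent fruit-and-vegetable substitution for high-fat foods in children, and says no comparable adult activity data are known. Coaches are also told to advise only the assigned changes.

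Finally, the article is condensed, and a composite pilot effect may exist in the full protocol. That cannot be excluded. But the article does set out a derivation, and that derivation does not yield a composite effect size.

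**Conclusion.** The point holds as a fault in the basis of the power statement, not in its arithmetic. Power of .85 for the composite is not established, because the .5 behind it matches an average of component effects and is not shown to be an effect on the composite.

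The error could go either way. Across the hypothesised arms, power is about .07 to .46 if untargeted components reverse, .39 to .98 if they are neutral, and above .95 if all four favour one arm. These ranges assume the pilot magnitudes in each arm, component SD 1 and a common correlation of 0 to .5, none of which the article confirms. Reversal is a plausible inference from the design, not a reported result.

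The conflict over sedentary time is firm: .5 against the article's own .21, with power of about .25 rather than .85.

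**What to change.** From the pilot data, compute the composite change score for each participant and report the signed one-versus-other-three effect for each arm. Put those values in place of .5 and restate the power at 50 vs 150.

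If the pilot composite cannot be obtained, withdraw the .85 claim for the composite and state the detectable effect instead: about .49 SD of composite change at .85 power, two-sided .05.

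In either case, restate the power for sedentary time at its own pilot effect of .21, and drop the statement that about .5 applies to every outcome.

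The cost is a re-analysis of pilot data and a revised paragraph. The stated power may become less favourable. No extra participants are required by this change.

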#### Secondary Aim: Behavioral and Psychological Processes

Whether participants adhere to each prescription can be verified by consumption elasticity: the degree to which each targeted behavior changes in response to prescription. Again using pilot data, we compared the target behaviors' elasticity for any one condition to the average elasticity of target behaviors for the other three conditions and found a mean difference of .437 (sd = .25) in elasticity, which yields an effect size of 1.78 to detect differences in adherence between one condition and all others. Given the effect size, our projected sample size of 50 per group should be adequate to detect differences in adherence across the planned contrasts. Our hypotheses also lead us to be interested in detecting differences between prescriptions in the magnitude of healthy substitution. Based on pilot data, we found a mean difference of .11 (sd = .08) in substitutability when we compared any one condition to the other three, which yields an effect size of 1.46. For an effect size of 1.46 a total of 50 subjects should suffice to test the contrasts.

Relevant outcomes are mood, craving for unhealthy foods and activities, and attentional allocation toward them. Mood will be measured daily during baseline and prescription phases, while craving and attentional allocation to unhealthy temptations will be measured during the two laboratory sessions. Based on pilot data, we found mean differences of 2.108 (sd = 6.057) for POMS vigor and 3.627 (sd = 10.275) for POMS dysphoria when we compared any one group to the other three. Based on the effect size estimates of .34 on vigor and .35 on dysphoria a sample size of 50 participants per group should yield adequate power.

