The behavioral economic Want Task will be administered next at both laboratory sessions to measure the relative reinforcing value of healthy and unhealthy foods and activities. On each of the Want Task's 40 trials, participant will be given $4 to allocate across 15 g portions of food and 1 minute portions of activity. The relative price per unit of each commodity will vary: $0.25, $0.50, $1, $2, and $4. Participants will be advised to spend all of the money they are given, since none can be saved or taken home. Data will be scored to yield the following four outcome variables: 1) amount *purchased *of healthy/unhealthy commodities, 2) amount *consumed *of healthy/unhealthy commodities, 3) own-price elasticity/inelasticity (the degree to which participants' consumption of a good is influenced by price change for that good), and 4) cross-price elasticity/inelasticity (the degree to which participants' consumption of a good is influenced by price change for another good, resulting from substitution or complementarity).

Throughout the baseline and prescription phases participants will also report their mood and hunger. Daily, just after completing the end-of-day activity log, they will rate their hunger on a 1-10 scale and describe their mood using the Positive and Negative Affect Schedule (*PANAS*) [41].

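### Fifty per group is called adequate for mood at effect sizes .34 and .35, but on the section's own settings power is about .55 and .57, and the effects come from the POMS while the trial uses the PANAS

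*Protocol article*

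**What the plan says.** The opening of Sample Size and Power says that the calculations "assume a two-sided alpha set at .05 and were estimated for a power of .85". Nothing in the section gives another alpha or power target for the secondary aim.

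Under Secondary Aim: Behavioral and Psychological Processes, the section reports pilot "mean differences of 2.108 (sd = 6.057) for POMS vigor and 3.627 (sd = 10.275) for POMS dysphoria", obtained "when we compared any one group to the other three". It then concludes, from "effect size estimates of .34 on vigor and .35 on dysphoria a sample size of 50 participants per group should yield adequate power".

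For the primary aim, the effect size is taken as .5, and the section says that "a total of 200 participants, 50 per group, will yield adequate power for testing the three contrasts".

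Under Psychological and Behavioral Process Measures, participants give daily ratings through baseline and prescription in which they "describe their mood using the Positive and Negative Affect Schedule" (PANAS). The POMS is not among the measures listed for the trial; it appears only in the power paragraph. The Analytic Plan assigns the psychological outcomes a linear mixed model with condition and time.

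**The concern.** The primary aim needs an effect of about .5 for 50 per group to be enough. The mood paragraph applies the same group size and the same judgement of adequacy to effects about 30% smaller (.35/.5 = .70; .34/.5 = .68). Both cannot hold under one alpha and one power target unless the mood analysis has some extra precision, and none is described.

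The second difficulty is the source of the effects. They are for two POMS scales, and the article gives no reason to expect the same standardised differences on the PANAS.

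At stake is how far a reader can rely on the mood comparisons of the secondary aim. The article presents them as adequately powered, and its own inputs do not show that.

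**Working it through.** **Inputs (all from the protocol article)**
- Two-sided alpha .05, target power .85: opening of Sample Size and Power.
- 50 per group, four groups, 200 in total: Primary Aim paragraph of that section.
- Contrast: one group against the other three, so 50 against 150.
- Mood effects: .34 (vigor) and .35 (dysphoria).
- Dropout: the power section states no allowance. I take none, which is the case most favourable to the plan.

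**Step 1. Effect sizes from the pilot figures.**
- Vigor: 2.108 / 6.057 = .348 (printed as .34).
- Dysphoria: 3.627 / 10.275 = .353 (printed as .35).

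These are mean differences divided by an SD, so they are standardised differences d. They are not Cohen's f, which would imply power above .98.

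**Step 2. Method.** The standard error of the contrast in SD units is sqrt(1/50 + 1/150) = .1633. The noncentrality is d / .1633. Power is taken from the noncentral t with 196 df (200 participants minus 4 groups) at two-sided .05.

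**Step 3. Reproduce the primary-aim statement.** For d = .5 the noncentrality is .5 / .1633 = 3.06 and power is .861. This agrees with the target of .85, so the method fits the plan's own reasoning.

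**Step 4. Apply it to mood.**

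| d | Noncentrality | Power |
|---|---|---|
| .34 (vigor, as printed) | 2.08 | .545 |
| .35 (dysphoria, as printed) | 2.14 | .569 |
| .348 (vigor, unrounded) | 2.13 | .564 |
| .353 (dysphoria, unrounded) | 2.16 | .576 |

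The normal approximation gives .549 and .573 for the printed values.

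**Step 5. What 50 per group can detect.** The smallest d is .49 at .85 power and .46 at .80 power. Both mood effects lie below either value, so reading adequate as the common .80 does not help.

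**Step 6. Sample size these effects would need.** By the noncentral t, .85 power needs 105 per group at .34 and 99 at .35 (104 and 98 by the normal approximation). These figures show the size of the gap; they are not a proposal to enlarge the trial.

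**Step 7. Other readings of the contrast.**
- 50 against 50: .39 and .41.
- 100 against 100: .67 and .69.
- One-sided test, 50 against 150 (normal approximation): .67 and .69.

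None reaches .80.

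**Step 8. Instrument.** Planning effects: POMS vigor and POMS dysphoria. Trial measure: PANAS. The article gives no conversion, no pilot PANAS figures and no argument that the effects carry over.

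**The case against.** The strongest reply is that a comparison with one measurement per person understates the planned analysis. Mood is rated daily over two baseline weeks and three prescription weeks, and the model is longitudinal. The article does not say whether the pilot SDs are for a single day, an average or a change score. The answer depends on that, and the correlations below are assumptions, since the article gives none:
- Raw-score SDs with adjustment for baseline (SD multiplied by sqrt(1 - r²)): power .67 and .69 at r = .5, and .83 and .85 at r = .7.
- Single-day SDs with 21 prescription days averaged (SD multiplied by sqrt((1 + 20r)/21)): .89 and .90 at a between-day correlation of .4, .82 and .84 at .5, and .69 and .71 at .7.
- SDs that already refer to change or to averages: the gain from that step is already counted, and .55 and .57 stand if nothing further is gained.

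This part stands: .55 and .57 are conditional figures. A reader might infer that they are the trial's real power for mood. The documents do not support that, both because a repeated-measures gain is possible and because POMS effects do not establish power for the PANAS. The reply does not rescue the sentence, however, because the article invokes no such gain and gives no correlation.

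A reader might also go further in three ways that the documents do not support:
- That a null mood result will be misread as no difference, or that the mediation analysis depends on this claim. No section plans such an interpretation of a null result. Mediation belongs to the exploratory aim and carries no power claim.
- That power should be computed at alpha .05/3 for the three contrasts. The article sets alpha at .05 and, for the primary aim, tests contrasts only after a significant omnibus test; it says the secondary analyses follow the same lines. It specifies no such split.
- That the mood comparisons must be relabelled as estimation only. That is a preference about reporting and does not correct an error.

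**Conclusion.** The statement that 50 per group is adequate for mood is wrong on the section's own terms. With two-sided alpha .05, 50 against 150, no dropout and no gain from baseline or repeated ratings, power is about .55 at .34 and .57 at .35. The shortfall against .85 is 28 to 30 points under those assumptions (.85 - .57 = .28; .85 - .55 = .30). A baseline correlation of about .7 on a raw-score SD, or a comparable gain from averaging days, would close most or all of it, but neither is stated. Separately, the planning effects belong to an instrument that the trial does not list, so power for the PANAS outcomes is not established at any value.

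The point is limited to a secondary outcome. A reader might infer that the trial is too small; the article does not support that, because its size is justified by the primary aim at an effect of .5, and that claim reproduces at .86. The correction should be made, but nothing in the primary analysis depends on it.

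**What to change.** In the Secondary Aim paragraph of Sample Size and Power:
- Replace the adequacy statement for mood with the figures: power of about .55 (vigor) and .57 (dysphoria) at the POMS-based pilot effects, without any gain from baseline adjustment or repeated measures, and a detectable effect of about .49 at .85 power with 50 per group.
- If such a gain is relied on, say what the pilot SDs refer to, state the assumed correlation, and give the resulting power.
- Reconcile the instruments: either state that the planning figures come from the POMS while the outcome is the PANAS, or use pilot PANAS figures if they exist.

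The change is to the text only. Sample size, allocation, conduct and the primary analysis stay as they are. The cost is a less favourable stated power for a secondary outcome.

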## Discussion

Considerable evidence links poor quality diet and physical inactivity not only to adverse health consequences [1-3] but also to each other. That is, poor quality diet and physical inactivity are characterized by a pattern of co-occurrence or multi-behavioral morbidity [9-11]. Being able to reduce bundled risk behaviors simultaneously would create the potential to do greater good, in less time, with less effort, and at less cost. The ability to efficiently capitalize on teachable moments for behavior change would be advantageous for health care providers, patients, and policy makers. Yet, despite the strong appeal of multiple behavior change interventions, a paucity of research demonstrates their feasibility let alone their success. The Make Better Choices study was designed both to address the feasibility of changing diet and activity behaviors simultaneously, and to identify the optimal combination of goals to maximize overall behavior change.

Here we have described the Make Better Choices design and procedure. The MBC RCT will randomize 200 sedentary adults with poor quality diet to improve one category of unhealthy dietary behavior and one category of unhealthy physical activity behavior simultaneously. Participants will be prescribed one of four interventions that recommend all possible combinations of increasing healthy and decreasing unhealthy diet and activity options. Healthful change will be assessed for both targeted and untargeted (collateral) behavioral outcomes.

This design will permit us to evaluate three alternative hypotheses: 1) *familiarity*, which predicts best outcome from prescribing usual dieting behaviors (↓FAT ↑PA);2) *behavioral economic*, which predicts best outcome from the condition that maximizes substitutive and complementary healthy change in both targeted and untargeted behaviors(↑FV ↓Sed); and 3) *low inhibitory demand *, which predicts best outcome from the condition that minimizes inhibitory demands (↑FV↑PA).

The mechanisms that underlie successful simultaneous change in health risk behavior bundles remain poorly understood. An important, novel feature of this research is the examination of change in collateral behaviors not targeted directly by an intervention. Examination of effects on untargeted outcomes is usually undertaken in order to identify unintended adverse consequences of an intervention. Here, instead, we examine whether untargeted healthy behavior changes can be harnessed effortlessly and to advantage.

Another key innovation in MBC involves the evaluation of a handheld PDA decision support tool that facilitates self-monitoring and remote communication with a behavioral coach. The use of technology that supports in vivo self-monitoring and timely distance coaching affords a potentially scalable, cost effective way to support health behavior change.

Limitations on the generalizability of study results warrant consideration. The requirement that enrollees persist in displaying all four risk behaviors despite throughout a baseline period will likely bias the sample towards those with severe multi-behavioral morbidity. Whether outcomes would differ in those with less recalcitrant or pervasive lifestyle risk behaviors warrants examination. Further, because MBC is designed to examine the feasibility and success of a new intervention under ideal conditions, participants will be paid to participate. It cannot be assumed that comparable outcomes would result in the absence of financial incentives.

In sum, the MBC study represents an important step toward identifying and improving strategies to address bundled health risk behaviors. The trial will permit hypothesis testing about optimal intervention to promote simultaneous diet and activity change. The high prevalence of health risk behaviors, the human and financial costs associated with chronic disease, and our poor understanding of how to reduce risk behaviors most efficiently all suggest the importance of the study.
